#### 2.2.3. The control condition

Those in the control condition will receive the MOSAIC intervention without the added IPT component. Participants in the control condition will also receive ongoing monitoring of depressive and PTSD symptoms and suicide ideation with appropriate referrals from mentor mothers. They will also be provided a county-specific IPV resource guide after consenting to enroll in the study.

#### 2.2.4. Randomization

Randomization to MOSAIC Plus or MOSAIC interventions will occur after the baseline assessment, in a 1:1 ratio. All baseline assessments are blind. Immediately after randomization, the research assistant will review the study outcome assessment schedule, means of contacting the research staff, and participants’ contacts with all participants. The study statistician will prepare the randomization schedule using opaque sealed envelopes before the enrollment of the first participant.

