#### 2.2.2. The MOSAIC Plus intervention

The MOSAIC Plus intervention will be delivered to those in the intervention arm as specified in the manual, for the duration of 9 months. After completing the screening interviews, the study research assistant will introduce consenting, eligible participants to a MOSAIC Plus trained mentor mother (See training procedures below). The mentor mothers will work as a mentors and advocates in the areas of IPV safety planning, building social support, managing depressive symptoms and enhancing effectiveness obtaining community resources. During the initial phase, mentor mothers will explain their roles as a MOSAIC Plus intervention provider and exchange contact information (i.e., the participant’s contact information and the mentor mother’s study cellphone number). In the following four weeks, the MOSAIC Plus mentors will meet their clients in a private, confidential location to assess if there is ongoing IPV, conduct safety planning, strength and needs assessment. They will collaboratively set a realistic treatment plan for the intervention period. MOSAIC Plus mentor mothers will maintain regular contact with their clients at least once a week (may be more as needed). Information obtained during initial assessment (safety, strengths, needs) will be used to plan the rest of the mentoring intervention in the subsequent months.

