#### 2.2.8. Assessments

The main goal of this pilot study is to explore the feasibility and acceptability of the MOSAIC Plus intervention. We will also evaluate the feasibility of the research and training procedures. In addition to these main outcomes, we will conduct several assessments to evaluate changes in depressive and PTSD symptoms, reduction in future IPV and changes in effectiveness in obtaining community to resources. The study research assistant (RA) will be trained to fidelity to administer clinical and other assessments. The clinical training process will also be supplemented by standard case vignettes showing elevated depressive and PTSD symptoms to acquaint trainees with common manifestations of IPV, symptoms of depression and PTSD. We will record all RA interviews and do regular quality and fidelity monitoring. Study mentor mothers will not play a role in the data collection process. Data will be collected at baseline, 3 months, 6 months and 9 months (post-intervention completion) (see Table 1: the SPIRIT schedule). We selected the following feasibility, acceptability, and safety metrics based on face validity, clinical experience, and relevant literature.

**Table 1 pone.0267679.t001:** Target outcomes.

Assessment method	Target

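### Blinding is declared only for baseline, and the research assistant role that administers the assessments also introduces intervention-arm women to their MOSAIC Plus mentor, so the follow-up assessor can learn the arm

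*Protocol article*

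**What the plan says.** Four parts of the Protocol article bear on this.

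- **Section 2.2.4 (Randomization)** sets the order: "Randomization to MOSAIC Plus or MOSAIC interventions will occur after the baseline assessment, in a 1:1 ratio". It then gives the article's single statement on blinding, followed at once by the assistant's contact with participants: "All baseline assessments are blind. Immediately after randomization, the research assistant will review the study outcome assessment schedule", along with contact arrangements, for women in both arms. On concealment it says: "The study statistician will prepare the randomization schedule using opaque sealed envelopes before the enrollment of the first participant". It does not say who opens an envelope.
- **Section 2.2.2 (The MOSAIC Plus intervention)**, which describes the intervention arm, says that after screening "the study research assistant will introduce consenting, eligible participants to a MOSAIC Plus trained mentor mother".
- **Section 2.2.8 (Assessments)** says: "The study research assistant (RA) will be trained to fidelity to administer clinical and other assessments". The assistant's interviews are recorded and monitored for quality, and mentor mothers take no part in data collection. On timing: "Data will be collected at baseline, 3 months, 6 months and 9 months".
- **Table 1** lists acceptability, working alliance and satisfaction as targets measured in MOSAIC Plus participants only.

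**The concern.** Knowledge of the arm can affect an outcome only after an arm exists. The visits at risk are therefore those at 3, 6 and 9 months, and the article declares none of them blind. It also gives one role two tasks that work against each other: a hand-over that is specific to the MOSAIC Plus arm, and administration of the assessments.

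An assessor who knows the arm may prompt, probe or reassure differently. Disclosure of partner violence on the CAS is sensitive to how the question is put, and symptom scales that are read aloud are open to the same influence. At stake are the between-condition effect sizes and 95% CIs of section 2.2.10, which are meant to suggest what a future trial could reasonably expect. The abstract goes further and calls symptom change the primary outcome. The Discussion says that the study pilots research procedures for the larger trial, so a weak assessment procedure could be carried forward.

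**Working it through.** The article states no figure on this point, so there is none to reproduce. The check is a reading of the relevant sections side by side, followed by one illustrative calculation.

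**Who can learn the arm, and when**

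1. Baseline comes first and randomization second (2.2.4). At baseline there is no arm to be blind to. Blinding at that visit can protect enrolment and baseline scores from a foreseen allocation, but it cannot protect a follow-up comparison.
2. The introduction to a MOSAIC Plus mentor is for women in the intervention arm (2.2.2), so it must follow allocation. The research assistant makes it. If the introduction is specific to that arm, the assistant learns who is in MOSAIC Plus and, by exclusion, who is in MOSAIC.
3. The research assistant role administers the assessments (2.2.8). The article names no second role for follow-up.
4. Taking 1 to 3 together, the roles as written allow the follow-up assessor to know the arm, and no stated safeguard prevents it.
5. There is a second route. If the assistant also collects the measures that Table 1 confines to MOSAIC Plus participants, giving them to a woman identifies her arm, whoever opened the envelope.
6. The authors did separate delivery from measurement, since mentors collect no data (2.2.8). They did not separate hand-over from measurement.

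**Illustration of size**

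Inputs: 20 women per arm (2.2.10), and an assumed assessor-induced shift of 0.2 SD between arms. The shift is not a document figure, so half and double that value are shown too.

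Approximate 95% CI half-width for an unadjusted standardized difference near zero: 1.96 × √(2/20) = 1.96 × 0.316 = 0.62.

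| Assumed shift (SD) | Share of half-width |
|---|---|
| 0.1 (half of 0.2) | 0.1 / 0.62 = 0.16 |
| 0.2 | 0.2 / 0.62 = 0.32 |
| 0.4 (double 0.2) | 0.4 / 0.62 = 0.65 |

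The interval reflects sampling error only, so a shift of this kind would move its centre without widening it. The table shows scale and is no evidence that such a shift would occur.

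**The case against.** The strongest reply is that the article is silent on follow-up blinding, and that silence in a condensed article is not a decision to leave assessors unblinded. Much of this stands. A reader might infer the following stronger claims, which the document does not support.

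- *The assistant is present at allocation or opens the envelope.* Section 2.2.4 places the assistant's contact after randomization, and the tasks listed are the same in both arms and need no knowledge of the arm.
- *The assistant hands every woman to an arm-specific mentor.* The introduction is described for MOSAIC Plus only. Section 2.2.6 trains the 8 mentors in both interventions, so a mentor's identity need not reveal the arm.
- *Follow-up is collected unblinded.* No section says so. Section 2.2.8 also mentions trainees, so more than one assessor is possible, and the full protocol may name a blinded one.
- *Baseline blinding is worthless.* Baseline scores on the PHQ-9, DTS and CAS decide eligibility and serve as covariates. Scoring them without foreknowledge of allocation has value, though not for follow-up.
- *Retention targets are biased between arms.* The targets in Table 1 (80% at 3 months, 70% at 6 months) apply to all participants pooled, and no between-arm comparison of retention is stated.

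Mitigating features also count. The PHQ-9 and DTS are self-report, interviews are recorded and monitored, both arms receive active mentoring, and the article says that the pilot is underpowered for firm conclusions and has feasibility as its main goal.

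The reply does not remove the point. The article does address blinding, confines it to baseline, and assigns tasks that work against blind follow-up. Self-report is only partial protection, because the eligibility criteria in 2.2.1 anticipate instruments being read aloud.

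**Conclusion.** The concern holds in a limited form. The only declared blinding covers a visit that precedes randomization, and the stated roles let the person collecting follow-up outcomes learn the arm without a stated safeguard. That is a conflict between assigned tasks, not just an omitted detail. It is not shown that follow-up is open or that any outcome would be biased.

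The conclusion assumes that the research assistant of 2.2.2 and of 2.2.8 is the same person, or people who share knowledge of the arm. If the full protocol names a separate blinded assessor, the matter reduces to stating that in the article. The size of any bias cannot be derived from the document. Because the effect sizes are exploratory with wide intervals, this is a worthwhile, inexpensive improvement and does not threaten the pilot's feasibility aims.

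**What to change.** 1. Have an existing team member who does no assessments open the envelope and make the mentor introduction in both arms. Amend 2.2.2 and 2.2.4 accordingly.
2. State in 2.2.4 or 2.2.8 that the 3-, 6- and 9-month assessments are done blind to arm.
3. Collect the MOSAIC Plus-only acceptability, alliance and satisfaction measures, and the exit interviews, after the outcome interview or through non-assessing staff. Without this step, the first two would not keep the assessor blind.
4. Have the assessor record a guess of allocation at 9 months, so that the extent of unblinding is measured.
5. If blinding cannot be kept, state that follow-up is unblinded and interpret the effect sizes of 2.2.10 with that caveat.

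The cost is a short task moved between existing staff, some scheduling effort, one added item at 9 months and a few edited sentences. Some women will still reveal their arm, and the guess in step 4 helps to show how often the assessor knew it.

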#### 2.2.5. Rationale for choice of target mechanisms

*2*.*2*.*5*.*1*. *Social support reduces IPV*, *depressive*, *and PTSD symptoms*. IPT’s focus on building social support is a good fit for mothers who have experienced IPV because social support is protective against the negative effects of partner violence [42, 43]and can help reduce future IPV [44, 45]. Perinatal women mothers with ongoing experience of IPV often struggle establishing social networks [43] and therefore additional help developing social support is useful. Social support also helps with depressive and PTSD symptoms [42]. Lack of social support is associated with antepartum depressive symptoms [44]. Studies suggest that social support, received in the form of informational, instrumental and emotional support, reduces depressive and PTSD symptoms in women with IPV experience [5, 42, 45]. Studies in population-based samples of women have found that women with experience of IPV with stronger social support are protected against the negative effects of IPV on mental health including depression and PTSD [42, 46]. In contrast, lack of perceived social support is a primary risk factor for developing PTSD following a traumatic experience [47–52]. Therefore, social support is a hypothesized target mechanism of the effects of MOSAIC Plus on IPV and mental health outcomes. The SPIRIT schedule is presented in the Fig 1 below.

**Fig 1 pone.0267679.g001:**
[figure not shown]
The SPIRIT schedule.

#### 2.2.6. Mentor mother training, supervision and supervision

We will recruit 8 mentor mothers and train them to deliver the MOSAIC and the MOSAIC Plus intervention with fidelity. Turnover in community interventionists can be high. Therefore, by training 8 mentor mothers, the study is likely to have at least 6 for the trial. If needed, additional mentor mothers can be recruited and trained. Mentor mothers will be selected with the help of our Community-Based Organization Partners (CBOP), our community partner for this study. With the support from CBOP and its network of partners, we will identify and interview women from Flint Genesee County. Mentor mothers will be: 1) 21 years of age and above, 2) have good listening skills and embody a non-judgmental attitude, 3) a permanent resident in Genesee County, 4) report that they are able to use a computer to upload intervention recordings and have access to a computer with internet, 5) are mothers, 6) have access to reliable transportation and 7) are available up to 2 hours per week by phone or in person. Mentor mothers will have weekly group supervision and case discussion with [name]. [name] will also listen to audio recordings of the mentor mother intervention sessions and will provide feedback. During weekly supervision or in the audio files, if a mentor appears to be triggered by a case discussion or talks about being overwhelmed in a group supervision meeting, [name] will promptly schedule an individual meeting and debrief session with the mentor mother. Mentor mothers will be constantly reminded that if they are feeling overwhelmed by a case (eg., thinking about the case more than they want to, poor sleep, changes in appetite, dreaming about the case, feeling anxious) they will be encouraged to contact [name] for a debrief and supportive supervision.

*2*.*2*.*6*.*1*. *Safety*. We will give strong emphasis to the safety of the mentor mothers. Briefly, we will develop a comprehensive protocol, based on the protocols used successfully in previous MOSAIC studies [24, 53], that covers safety planning with the client and procedures to ensure safety of the mentor mothers. Contents of the protocol will involve leaving the scene if there is an apparent violence and procedures for immediate reporting of any safety concerns and questions. Mentor mothers will be given a study cellphone to communicate with their clients. They will meet their clients in public places with private space such as health facilities, libraries and parks to reduce potential risk of victimization. To protect mentor mothers’ privacy, mentor mothers will not share their residence addresses and last names with their clients. We will train mentor mothers on how to respond to clients’ substance abuse. Moreover, safety plans will be adapted and tailored to each participating woman based on her needs. Mentor mothers will also be trained on burnout management, self-care and will be offered an opportunity to debrief with study investigators quarterly, and to call on an as needed basis.

#### 2.2.7. Fidelity ratings

Intervention adherence and competence ratings will be developed based on the manual and previous IPT adherence and competence scales [30, 54]. Adherence rating scales for both conditions will consist of a checklist of tasks to be completed at each meeting. Competence rating scales will be completed from audio recordings of mentor mother visits and will reflect mentor mothers’ general skills, such as reflective listening, safety planning, linking women to services, advocacy and effective goal setting. The study team will use these scales to rate a randomly selected 33% of the open trial tapes. Scale development will continue until the item content is satisfactory and interrater reliability is acceptable (> .80). Fig 2 below shows the study flow chart.

**Fig 2 pone.0267679.g002:**
[figure not shown]
The MOSAIC Plus flow chart.

#### 2.2.8. Assessments

The main goal of this pilot study is to explore the feasibility and acceptability of the MOSAIC Plus intervention. We will also evaluate the feasibility of the research and training procedures. In addition to these main outcomes, we will conduct several assessments to evaluate changes in depressive and PTSD symptoms, reduction in future IPV and changes in effectiveness in obtaining community to resources. The study research assistant (RA) will be trained to fidelity to administer clinical and other assessments. The clinical training process will also be supplemented by standard case vignettes showing elevated depressive and PTSD symptoms to acquaint trainees with common manifestations of IPV, symptoms of depression and PTSD. We will record all RA interviews and do regular quality and fidelity monitoring. Study mentor mothers will not play a role in the data collection process. Data will be collected at baseline, 3 months, 6 months and 9 months (post-intervention completion) (see Table 1: the SPIRIT schedule). We selected the following feasibility, acceptability, and safety metrics based on face validity, clinical experience, and relevant literature.

**Table 1 pone.0267679.t001:** Target outcomes.

Assessment method	Target
**MOSAIC Plus Feasibility and Acceptability (MOSAIC Plus participants only)**	
Acceptability (End of Treatment Questionnaire)	Endorsing an average score of 3 or more (out of 5) for each rated intervention component).
Quality of working relationship (WAI-SR)	Average > 36 (or a mean score of 3 or more [out of 5] on each of the 12 items). We will also descriptively examine goal, tasks, and bond subscales to see where mentor mothers are doing well and less well overall.
Satisfaction (Client Satisfaction Questionnaire-8)	Average > 24 (or a mean score of 3 on each of the 8 items)
Intervention attendance	70% of all participants complete at the initial session and at least 2 of 3 booster sessions
Intervention Fidelity	MOSAIC Plus intervention achieves at least 80% adherence on a random subset of sessions

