After the initial phase is complete, as in the original MOSAIC intervention, mentor mothers will continue meeting their clients (in person or by phone) for a session no less than 60 minutes. This level of contact is high but was feasible and acceptable in the original MOSAIC trial [24]. In person meetings will take place in the community at convenient, private, and safe locations (libraries, treatment facilities, public buildings) as suggested by the clients. Telephone meetings will only be made from a study telephone line given to each mentor mother. The mentor mothers will review their clients’ activities since the initial planning meeting and problem-solve any challenges they may encounter. Mentor mothers also facilitate their clients’ access to other services by informing, educating and advocating for them when needed. Their services will involve 1) building social support networks by helping their clients solve any interpersonal difficulties they may have within their networks. Mentor mothers will also work with their clients by linking them with new social support groups and networks available in the community. They will focus on social support because strong social support protects against the negative effects of IPV on mental health [42]. 2) Mentor mothers will inform women about services and advocate for their access. Women with experience of IPV may have limited access to information, and hence poor access to services. Mentor mothers will help improve their access to services by actively identifying the needed services, creating proper linkage with providers and advocating for their access by addressing the barriers they may encounter. 3) Plan and monitor their safety by helping their clients create a personalized safety plan and monitor the potential of future violence and address any challenges they may have. Mentor mothers will employ the skills of active listening, reflecting and validating feelings, showing empathy, inspiring hope and facilitating a trusting relationship with other people in their personal networks or people who are service providers. The IPT component in this intervention includes the focus on addressing interpersonal conflict within the woman’s social network. MOSAIC Plus is consistent with the original intent of MOSAIC (support the mother directly), but utilizes a broader conceptualization (i.e., help the mother build her own social support network) and evidence-based IPT strategies for doing so.

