**Feasibility and Acceptability—Research Procedures (all participants)**	
Recruitment rate	Average of 4–8 enrolled per month
MOSAIC Plus intervention procedures	80% of participants complete MOSAIC Plus intervention sessions at 3 months and 70% at 6-month follow-up
Timeliness of assessments	80% of follow-up assessments occur within 3-weeks of due date
Completeness of self-report instruments and interviews	Self-report instruments have 80% of items completed and interviews 90% of items completed in 90% of cases
Retention rate	80% complete 3-mo and 70% complete 6-mo follow up assessments
Participant burden	Qualitative responses from exit interviews do not suggest undue burden of intervention or research procedures

*2*.*2*.*8*.*1*. *Demographic/screening measures*. Will include age, educational level, marital status, occupation, employment (status, # hours per week), income, race, gestational age/age of children. At follow ups, occupation, employment (status, # hours per week), and income will be repeated. We will also assess relationship information, such as current relationship to the abuser/s and length of relationship. We will use the Composite Abuse Scale (CAS) [37] to include women who report any physical and sexual violence in the past six months. We will also use the Patient Health Questionnaire (PHQ-9) with a cut-off point of ≥ 9 [55] and/or the Davidson Trauma Scale (DTS) with a clinical cut off point of ≥ 40 to determine eligibility in terms of depressive and/or PTSD symptoms [39].

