*2*.*2*.*8*.*2*. *Primary*: *Study Feasibility and Treatment Feasibility/Acceptability and safety*. We will assess feasibility of the research procedures by examining study recruitment and refusal rates, participants’ willingness to be randomized, follow-up rates, reliability and range of responses to study questionnaires. We will assess the feasibility and acceptability of MOSAIC Plus by examining treatment completion (based on the jointly established treatment plan) and drop-out. We will examine reasons for termination from study and/or intervention for consistent patterns. We will examine the acceptability of the MOSAIC Plus intervention by using data from CTQ-8 treatment satisfaction questionnaire, the End of Treatment Questionnaire, and detailed exit interviews. Clients’ experiences with the mentor mothers, the quality of their working relationship and their level of satisfaction with the service will be evaluated using the Working Alliance Inventory-Short Revised (WAI-SR). Moreover, as in the original MOSAIC study [34], we will also explore perspectives of the mentor mothers regarding acceptability of the MOSAIC Plus intervention. We will use Competency Assessment Inventory (CAI), which tests the attitudes, knowledge, and skills needed to provide high-quality mental health care (i.e., learns and respects clients’ preferences about intervention, creates opportunities for clients to practice skills).

At the end of the open trial and at 2 time-points during the RCT (i.e., after enrolling 20 and 40 participants), we will compute the descriptive data on all target outcomes described in Table 2. The scientific team will convene to discuss how our actual outcomes compare to target outcomes. If the team identifies discrepancies between target outcomes and actual outcomes, we will 1) investigate the reason for failure to meet the stated outcomes, and 2) discuss among the research team. Depending on the nature of the discrepancy, we may modify recruitment or assessment procedures, instructions to participants, training procedures, or other trial aspects. Table 1 below presents assessment methods.

**Table 2 pone.0267679.t002:** Target mechanisms.

Target Mechanism 1: Social support	
Definition	“Emotional, informational and practical assistance provided in a supportive social network” [69]
Evidence that adding IPT approaches increase social support	IPT has been found in many studies to increase social support relative to control conditions [70–73]

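### Two Table 1 feasibility targets, for attendance and completion, do not fit the MOSAIC Plus programme and two-arm design that the protocol describes

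*Protocol article*

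**What the plan says.** Sections 2.2.8 and 2.2.10 of the protocol article name feasibility and acceptability as the main goal of the pilot. Table 1 (Target outcomes) gives the numerical targets. Two rows concern how much of the intervention women take up.

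- **Attendance**, in the block headed "MOSAIC Plus Feasibility and Acceptability (MOSAIC Plus participants only": "70% of all participants complete at the initial session and at least 2 of 3 booster sessions".
- **Completion**, in the block headed "Feasibility and Acceptability—Research Procedures (all participants": "80% of participants complete MOSAIC Plus intervention sessions at 3 months and 70% at 6-month follow-up".

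The intervention itself is described elsewhere. Section 2.2 sets its length at 9 months in both arms. Section 2.2.2 has the mentor introduced to the woman, followed by four weeks of meetings for assessment and planning. It says that mentors "will maintain regular contact with their clients at least once a week (may be more as needed". After that phase, "mentor mothers will continue meeting their clients (in person or by phone) for a session no less than 60 minutes". Section 2.2.3 gives controls MOSAIC without the IPT component. Section 2.2.4 sets 1:1 allocation.

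Section 2.2.8.2 says that feasibility of MOSAIC Plus will be judged by "treatment completion (based on the jointly established treatment plan) and drop-out". It has the team compare actual with target outcomes at the end of the open trial and after 20 and 40 enrolments in the randomised trial.

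**The concern.** A feasibility target is useful only if its numerator and denominator can be counted in the trial being run. Here the attendance numerator refers to a session structure that appears nowhere else in the document. The completion denominator, taken from its block header, includes women who are not offered the sessions being counted. The attendance row has the reverse mismatch: it speaks of all participants under a header limited to MOSAIC Plus participants.

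Whether women keep up this level of mentor contact is a central question for the fully powered trial that the pilot is meant to inform. If the attendance target cannot be scored, that question gets no clear answer. If it is scored loosely, poor uptake could pass as success. A completion target computed on the wrong denominator would look missed however well women attended, and could prompt procedural changes that are not needed.

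**Working it through.** **Inputs.** 40 women randomised (section 2.2); 1:1 allocation (2.2.4); 20 per condition (2.2.10); 15 women in the open trial, all receiving MOSAIC Plus (2.1.5); 9-month intervention (2.2, 2.2.2); contact at least weekly (2.2.2); targets of 70% for attendance and of 80% and 70% for completion (Table 1).

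**The plan's own figure.** 40 × 1/2 = 20 per condition, as section 2.2.10 states. The 70% and 80% targets are set by judgement, so there is no derivation to reproduce.

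**Attendance row.** The row implies four sessions: one initial and three boosters. Section 2.2.2 has an introduction, a four-week phase of meetings and then continuing sessions. The introduction might be called an initial session, but nothing corresponds to three boosters. There are two ways to score the row:

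- Literally, no woman can attend a booster, so none can meet the target.
- Loosely, the first session plus any two later ones is 3 contacts. Nine months is 9 × 52/12 = 39 weeks, so weekly contact gives about 39 contacts, and 3/39 = 7.7%.

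The 39 is an assumption. The weekly-contact sentence stands with the description of the initial phase, and the later text gives a session length but no frequency. If contact were weekly for 4 weeks and then half as frequent for the remaining 35, the total would be 4 + 35/2 = 21.5, and 3/21.5 = 14%. The share stays small, and the mismatch does not depend on it.

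**Completion row, header read literally.** Only women assigned to MOSAIC Plus can complete its sessions. The highest possible percentage is therefore women offered MOSAIC Plus divided by all women counted.

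| Group counted | Highest possible | Target 80% | Target 70% |
|---|---|---|---|
| All 40 randomised | 20/40 = 50% | 32 needed | 28 needed |
| First 20 randomised, if split evenly | 10/20 = 50% | 16 needed | 14 needed |
| Randomised plus open trial | 35/55 = 63.6% | out of reach | out of reach |
| Open trial alone | 15/15 = 100% | 12 needed | 11 needed |

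For all 40, the MOSAIC Plus arm would have to supply 32/20 = 160% or 28/20 = 140% completion.

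**Completion row, MOSAIC Plus arm as denominator (n = 20).** The targets become 16/20 (exact 95% CI 56% to 94%) and 14/20 (46% to 88%). Both are attainable. If true completion equals the target, the observed proportion reaches it with probability 0.63 (80% target) or 0.61 (70% target).

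**Definition of completion.** The row gives no session count. Section 2.2.8.2 measures completion against each woman's jointly set plan. The document does not say whether the row applies that definition or another.

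**The case against.** The best defence concerns the completion row. Its own label and wording name MOSAIC Plus, so a sensible reader would count only women given MOSAIC Plus. At the first planned review, the end of the open trial, all 15 women receive it and the denominator problem does not arise. That stands: the 50% ceiling follows from the header read literally, and a reader who infers that the target can never be met goes too far. The header still needs correcting, because the randomised trial is where the two readings part.

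A reader might also infer that the pilot's feasibility criteria as a whole fail. They do not. The other four rows of the MOSAIC Plus block (End of Treatment Questionnaire, working alliance, satisfaction, fidelity) can be scored as written, and the remaining Table 1 rows are not touched by this point.

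Nor are these go/no-go thresholds. Under section 2.2.8.2 a missed target leads to investigation and discussion, after which the team may modify procedures. An automatic wrong decision is therefore not in prospect.

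The individual-plan definition is not shown to contradict the completion row, since the row could be a threshold on that very definition. What is missing is a statement that it is. It is also tempting to say that the booster wording came from another intervention, but the document gives no evidence of its origin.

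Nothing in this defence rescues the attendance row. The condensed form of a journal article does not explain it either, because a printed threshold conflicts with the printed programme.

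**Conclusion.** The point holds for two rows. The attendance target cannot be scored against the programme described. On a loose reading it would be met by about 8% of planned contacts, assuming weekly contact for all nine months and counting any two later sessions as boosters. The completion target, under its stated header, cannot exceed 50% in the randomised trial against targets of 80% and 70%. With the evident denominator it is attainable, but its link to the individual treatment plan is left open.

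The likely harm is an unclear result on uptake, or an unnecessary mid-trial change. This should be fixed, but it does not undermine the trial's feasibility assessment as a whole.

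**What to change.** 1. Delete the booster wording from the attendance row and restate the target in the session units of the MOSAIC Plus manual. Make the row's reference to all participants agree with its header. Table 1 and sections 2.2, 2.2.2 and 2.2.8.2 must be reconciled on session structure; which structure is right is for the investigators to settle.
2. Move the completion row to the block for MOSAIC Plus participants only. Use women assigned to MOSAIC Plus as denominator: 20 in the randomised trial, 15 in the open trial. Keep the 80% and 70% targets, which are 16/20 and 14/20 in the randomised trial.
3. Use one definition of completion in Table 1 and section 2.2.8.2, fixed before the first randomisation.

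The cost is an edit to two table rows and one sentence. The attendance criterion may become harder to meet than under a loose reading of the present wording.
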